### Data monitoring

An initial internal pilot phase assessed the feasibility of recruitment. An independent Trial Steering Committee (TSC) is overseeing the trial. The TSC determined at their first meeting that no separate Data Monitoring and Ethics Committee (DMEC) was required, as the TSC would also fulfil this remit.

Progression criteria were as follows:

Trial feasibility was based on recruitment of schools and students across the four sites with progression to a full trial in all sites dependent upon progress. Progression thresholds are set out in Table 2: 1) Green: continue to full trial without modification; 2) Amber: remediable issues; proceed with caution following review processes with the Trial Steering Committee and PPI group to; Red: early cessation, intractable issues. The decision to continue was made in May 2021.

**Table 2 Tab2:** Progression criteria for the Stand Together Trial

	Green	Amber	Red
% of target schools recruited	≥90%	80–89%	≤79%
% eligible students recruited	≥80%	60–79%	≤59%
% baseline primary outcome collected	≥90%	80–89%	≤79%
% of baseline secondary outcomes collected	≥80%	65–79%	≤64%

### Statistical methods

A detailed statistical analysis plan will be written prior to database lock. We will report trial outcomes following CONSORT guidelines for cluster RCTs [37] and the SPIRIT statement for trials of interventions [38]. This will involve a combination of quantitative and qualitative methods. Statistical analysis will be performed in Stata (version 63 or higher). All analyses will be intention to treat (ITT) (i.e., students will be analysed in the groups to which they were randomised, regardless of adherence to intervention) and missing outcome data will not be replaced (all main statistical analysis will be conducted on complete cases). Between-group comparisons will be presented with two-sided 95% confidence intervals (CI). As the trial includes a reasonable number of clusters, the analysis will be based on the individual student, allowing for clustering between students within school using robust standard errors. Analyses will control for the school level stratification variables (geographical area, school size, proportion of students eligible for Free School Meals (FSM)). Key student characteristics (age, sex) will also be controlled for.

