**Methods:**

Design: Two-arm pragmatic multicentre cluster randomised controlled trial with an embedded process and cost-effectiveness evaluation.

Participants: 116 primary schools from four areas; North Wales, West Midlands, South East and South West England. Outcomes will be assessed at student level (ages 7–11 years; n = approximately 13,000 students).

Intervention: KiVa is a whole school programme with universal actions that places a strong emphasis on changing bystander behaviour alongside indicated actions that provide consistent strategies for dealing with incidents of bullying. KiVa will be implemented over one academic year.

Comparator: Usual practice.

Primary outcome: Student-level bullying-victimisation assessed through self-report using the extensively used and validated Olweus Bully/Victim questionnaire at baseline and 12-month follow-up.

Secondary outcomes: student-level bullying-perpetration; student mental health and emotional well-being; student level of, and roles in, bullying; school related well-being; school attendance and academic attainment; and teachers’ self-efficacy in dealing with bullying, mental well-being, and burnout.

Sample size: 116 schools (58 per arm) with an assumed ICC of 0.02 will provide 90% power to identify a relative reduction of 22% with a 5% significance level.

Randomisation: recruited schools will be randomised on 1:1 basis stratified by Key-Stage 2 size and free school meal status.

Process evaluation: assess implementation fidelity, identify influences on KiVa implementation, and examine intervention mechanisms.

Economic evaluation: Self-reported victimisation, Child Health Utility 9D, Client Service Receipt Inventory, frequency of services used, and intervention costs. The health economic analysis will be conducted from a schools and societal perspective.

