### Schools and participants

One hundred and eighteen mainstream primary schools have been recruited (two more than planned).

Students in Years 3 to 5 provided baseline data from April–July 2021. The cohort of recruited students will provide follow-up data 12-months later when they are in Years 4 to 6 following the delivery of the KiVa programme for one academic year in intervention schools. Data will be collected from all eligible students, and school staff (teachers, higher level teaching assistants, and teaching assistants) in each arm at each time point. See Fig. 1 for the Stand Together study flowchart.

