#### Routinely collected data

At follow-up, participants’ parents will be provided with information and an opportunity to opt their child out from their child’s trial data to be linked with their routine education data. Children’s identifiers: Name, School, Year Group, DoB (where available), Gender (where available) will be provided by sites to enable this linkage. Education data will be requested from the NPD in England and student attainment dataset in Wales via their formal approval processes. Data requested will be related to some demographic information (Ethnicity, special educational needs), attendance, and academic attainment from the Key Stage 2 assessment to enable a comparison between trial arms. Data from the trial will be sent to the ONS Secure Research Service, a secure data safe haven used by the Department for Education and linked on a record level with the data from the NPD using the participant ID.

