#### Primary outcome

Multilevel logistic regression models will be used to compare the proportion of students reporting victimisation at 12 months post randomisation by arm, and results presented as odds ratios and 95% CIs. ICCs alongside 95% CIs will also be reported.

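### The covariates stated for the primary model leave out baseline victimisation, forgoing power and leaving chance baseline imbalance between arms uncorrected

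*Protocol article*

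**What the plan says.** The Statistical methods section of the Protocol article names the covariates. At school level: "Analyses will control for the school level stratification variables (geographical area, school size, proportion of students eligible for Free School Meals (FSM". At student level: "Key student characteristics (age, sex) will also be controlled for". Neither list is introduced as an example. The Primary outcome paragraph of the same section adds no baseline term: "Multilevel logistic regression models will be used to compare the proportion of students reporting victimisation at 12 months post randomisation by arm".

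The outcome is nevertheless measured twice. The Abstract describes it as self-report on the "validated Olweus Bully/Victim questionnaire at baseline and 12-month follow-up", and Table 1 schedules the questionnaire at both times. Schools and participants describes one cohort followed for a year and states: "Data will be collected from all eligible students, and school staff". Table 2 makes "baseline primary outcome collected" a progression criterion, with green at 90% or more. Baseline covariates are mentioned for the imputation models under Missing data, but not for the main analysis.

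Two further statements bear on the remedy. Main analyses use complete cases (Statistical methods). Under Blinding, schools could not all be kept unaware of allocation until every child baseline was in; this failed in about 60% of them. That section argues that children should have seen no sign of KiVa in that school year, and it plans to compare data collected before and after notification.

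**The concern.** A child's earlier report of being bullied, and the level of bullying in the school a year before, are natural predictors of the 12-month outcome. The trial collects both and uses neither in its stated primary model. At the design ICC most of the uncertainty in the arm contrast lies between schools, where a school-level baseline could help most. Randomisation was stratified on Key Stage 2 size and free-school-meal percentage, not on bullying, so nothing in the design balances baseline victimisation beyond what those factors achieve indirectly. If the arms differ at baseline by chance, the stated model cannot correct for it. At stake are efficiency and the credibility of the estimate, not the validity of the test.

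**Working it through.** **Inputs from the Sample size section.** 18% v 14% (22% relative reduction, i.e. 14.04%), 90% power, 5% significance, ICC 0.02, 111 students per school, 10% student dropout, one school lost per arm, 58 schools per arm. The analysed design is therefore 57 schools per arm with 111 × 0.9 = 99.9 students each.

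**The plan's own figures.**
- Individual level: (1.960 + 1.282)² × (0.18×0.82 + 0.14×0.86) / 0.04² = 1,760 per arm, or 3,520. This matches.
- Design effect: 1 + 110 × 0.02 = 3.2. Schools per arm: 1,760 × 3.2 / 0.9 / 111 = 56.4, rounded up to 57, plus one for dropout = 58, or 116 in all. This matches.
- Power with 57 schools per arm, 99.9 students each and 18% v 14.04%: 91.6%.

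The stated size and power are thus obtained with no credit for baseline adjustment.

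**Where the variance lies.** Per school, in units of p(1−p): 0.02 + 0.98/99.9 = 0.0298. The between-school share is 0.02/0.0298 = 67%.

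**Chance imbalance at baseline.** SE of the between-arm difference in baseline prevalence = √(2 × 0.18 × 0.82 × 0.0298 / 57) = 1.24 points, a 95% range of about ±2.4 points. The chance of a difference above 1 point is about 42%; above 2 points, half the target effect, about 11%.

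**Gain from adjustment.** The article gives no baseline-to-follow-up correlations, so these are assumptions: rc between schools, 0 to 0.7; ri between students within schools, 0.2 to 0.5. On the proportion scale,

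variance ratio = [0.02(1 − rc²) + 0.0098(1 − ri²)] / 0.0298.

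| ri | rc | ratio | power |
|---|---|---|---|
| 0.2 | 0 | 0.99 | 92.0% |
| 0.3 | 0 | 0.97 | 92.4% |
| 0.3 | 0.3 | 0.91 | 93.8% |
| 0.3 | 0.5 | 0.80 | 96.2% |
| 0.5 | 0.5 | 0.75 | 97.1% |
| 0.5 | 0.7 | 0.59 | 99.2% |

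The rows with rc = 0 show that little is gained unless baseline explains between-school variance.

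**Missing baselines.** If 10% of children lack a baseline and are dropped as incomplete cases, the ratio runs from about 1.02 (ri 0.2, rc 0: a small net loss) to 0.62, and is 0.84 at ri 0.3, rc 0.5.

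**If notification altered baseline reports.** Assume a 2-point shift in KiVa schools only, in 60% of them, applied to all their children. The adjusted effect moves by 0.6 × 2 × slope, where the slope of follow-up on baseline school means is (0.02·rc + 0.0098·ri)/0.0298.
- ri 0.2, rc 0.3: slope 0.27, bias 0.32 points.
- ri 0.5, rc 0.5: slope 0.50, bias 0.60 points.

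The unadjusted variance is 1.18² = 1.40 square points. In the first case adjustment saves 0.074 × 1.40 = 0.10 and the squared bias is 0.10. In the second it saves 0.25 × 1.40 = 0.35 and the squared bias is 0.36. A shift that large would use up the gain. A 1-point shift costs a quarter as much (0.03 and 0.09) and leaves most of it.

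**The case against.** The strongest reply is that this belongs to the analysis plan, which the article says will be written before database lock, and that adjusting for design factors, age and sex is already valid. The second part stands. The first does not remove the point: the article does not leave the covariates open but states them, and an unseen plan does not undo a stated list.

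A second reply is that the child baseline is not cleanly pre-allocation, so keeping it out of the primary model is cautious. This has weight. The calculation above shows that a 2-point shift would offset the gain at low correlations and, on the same arithmetic, at mid-range ones. But the shift is hypothetical, the Blinding section gives a reason to expect none, and the planned timing comparison together with a sensitivity model can contain the risk.

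Third, the size of the gain is assumed. Baselines were taken in April–July 2021, after the closures noted under Fig. 1, and school-level correlation with 2022 could be low. Area, size and free-school-meal proportion may already explain some between-school variance, which would make the added gain smaller than shown. Both caveats stand.

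Stronger readings that the article does not support:
- *The trial is underpowered.* Its figures reproduce without the baseline term.
- *The odds-ratio interval is wider than it need be.* The calculation is on the proportion scale. In a logistic model, adjustment also moves the odds ratio towards a more conditional one, so the gain appears as power and not necessarily as a narrower interval.
- *Every child has a baseline.* All eligible students are targeted, but parents may withdraw a child, children may decline, and green starts at 90%.
- *Age or sex will be missing from the model.* The wording "DoB (where available), Gender (where available) will be provided by sites to enable this linkage" concerns identifiers for linkage to education records, not the analysis dataset.

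**Conclusion.** The point holds as one of efficiency and robustness. The stated primary model omits an outcome-specific baseline that the trial collects on its own cohort. The 90% power claim is unaffected. The cost is a forgone variance reduction of about 1% to 41%, roughly 10% to 25% at mid-range correlations, and no correction for a baseline difference between arms whose standard error is about 1.2 points. The imbalance figure rests on the article's own prevalence, ICC and school numbers, taking the follow-up ICC to apply at baseline. The variance reduction rests on correlations that the article does not give, so there is more certainty about the omission than about its size. It should be changed, but leaving it would not invalidate the trial.

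**What to change.** Add two terms to the primary model: the child's baseline victimisation status on the global item, and the school's baseline victimisation prevalence. State a rule for missing baselines, either a missing indicator or simple imputation, so that complete-case analysis loses no follow-up respondent for want of a baseline.

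Prespecify the same model without the two baseline terms as a sensitivity analysis, to be read beside the before-and-after-notification comparison already planned under Blinding.

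The cost is a few sentences in the analysis plan before database lock; no new data are needed. The downside is a slight bias if notification changed baseline reports in KiVa schools: about 0.3 to 0.6 points for an assumed 2-point shift and slopes of 0.27 to 0.5, against the 4-point target. A clear difference between the two models would be the signal to report that risk openly.

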#### Primary outcome

Multilevel logistic regression models will be used to compare the proportion of students reporting victimisation at 12 months post randomisation by arm, and results presented as odds ratios and 95% CIs. ICCs alongside 95% CIs will also be reported.

#### Secondary outcomes

Multilevel linear (continuous outcomes) and logistic (binary outcomes) regression models will be used to compare secondary outcomes.

#### Sub-group analyses

These will investigate the effect of the intervention by student sex and FSM status. Interactions will be modelled between the study arm and these variables. The results of these exploratory analyses will be presented using 95% CIs.

#### Missing data

To investigate the impact of any missing outcome data on the trial conclusions, missing mechanisms will be explored, and appropriate imputation methods applied via sensitivity analyses. Baseline characteristics will be compared with post-randomisation variables of students who have and have not completed primary outcome data. Multiple imputation will be performed to assess the impact of missing outcome data using the mi command in Stata. Imputation models will include outcomes (including student attendance), intervention arm, stratifying variables, and a main school effect to allow for clustering, as well as any appropriate baseline covariates. The main analyses will be repeated on the imputed datasets. As an added sensitivity analysis, a scenario-based imputation will be carried out such as best-worst case scenario assuming all lost to follow up in the KiVa arm have been victimised and vice versa.

#### Intervention compliance

The effect of KiVa lesson dosage on the primary outcome will be explored in a sensitivity analysis and estimated in a way that preserves randomisation using Complier-Average Causal Effect (CACE) estimates, using a two-stage least squares instrumental variable regression model Dunn [39].

#### Qualitative analysis

With appropriate consent, all interviews and focus groups will be audio-recorded, transcribed fully, and pseudonymised for analysis. Computer software (NVivo) will be used to manage the qualitative data and transcripts. Thematic analysis [40] will be used to analyse each of the sub-sets of interviews/focus groups (school staff, pupils, parents/carers) separately and independently. A thematic analysis approach will be used for a qualitative synthesis across the interview/focus group sub-groups. This analysis will then provide an over-arching synthesis of school staff, pupils’ and parents/carers’ experiences and perceptions related to the process evaluation aims. Where appropriate (e.g., where both school staff and parents/carer discuss the same issue – e.g., school context) we will examine the data and the extent to which the views of these groups are aligned.

A Qualitative Analysis Plan (QAP) will provide further detail on the approach and steps which will be taken to the analysis of the qualitative data from the process evaluation.

#### Triangulation of qualitative and quantitative data

A triangulation exercise will be conducted combining all of the qualitative results with the quantitative data analysis results including school recruitment, implementation fidelity, intervention mechanisms and their interaction with local context. Data collection across the study will be designed to maximise the potential for triangulation.

We will draw on Palinkas et al’s (2011) taxonomy of mixed methods designs to guide triangulation of data collection and analysis [41].

### Cost-effectiveness

The full cost of delivery of the KiVa intervention and associated costs will be calculated. The health economic analysis will be conducted from a schools and societal perspective [42–44].

Taking into account National Institute of Health and Care Excellence guidance on economic evaluations of public health interventions [45] and the effects of clustering [46], we will undertake a primary cost effectiveness analysis of the KiVa intervention, using student self-reported quality of life (CHU-9D) as the outcome of effect [42–44]. Costs calculations will include the time and resources required to implement KiVa in schools, including the cost of any training. This information will be collected from CEIT, the UK KiVa programme trainers, and KiVa team members in intervention schools. Staff salary costs will be calculated using national sources (National Union of Teachers Salary Card, 2018) [47]. Cost and quality of life data will subsequently be combined to calculate an incremental cost-effectiveness ratio (ICER), which will report the cost per unit of effect (i.e., cost per quality adjusted life year using KiVa compared to the control condition) [42–44]. We will also be interested in the proportion of children moving from “bullied” to “not bullied”, over the study period in each condition compared with the marginal cost of delivery of KIVA in schools.

We will also embed a wider cost consequence analysis [42] to explore self-reported bullying incidences using OBVQ data along with other outcome measures collected for both students and teachers [25].

A fully documented Health Economics Analysis Plan (HEAP) will be written based on published guidance for best practice [48], aligning with the Statistical Analysis Plan, and agreed by the co-applicants before follow-up data collection has been completed, as the HEAP is intended as a living document to incorporate any changes or updates as the trial progresses. This plan will be locked before any analysis is undertaken. The cost-effectiveness analysis will be reported according to the Consolidated Health Economics Evaluation Reporting Standards.

### Ethical approval and consent to participate

Ethical approval was granted by Bangor University Psychology Research Ethics and Governance Committee (2019–16,592) on 13th November 2019.

### Amendments to ethical approval

There have been 12 minor amendments to our original Ethics application, which include minor revisions/additions to information sheets and consent forms, minor changes to the protocol such as the addition of questionnaires for teachers and the inclusion of covid procedures as well as forms for the process evaluation element of the trial. There was also the inclusion of a sub-study to explore pupils’ social and emotional wellbeing and changes in bullying behaviour and relationships over time. The list of amendments with approval dates are as follows:

**Table Taba:** 

2019–16,592	Original application approved 13/11/19
2019–16,592-A14604	Amendment approved 28/11/19
2019–16,592-A14613	Amendment approved 17/12/19
2019–16,592-A14627	Amendment approved 27/01/20
2019–16,592-A14631	Amendment approved 27/01/20
2019–16,592-A14662	Amendment approved 24/03/20
2019–16,592-A14668	Amendment approved 09/04/20
2019–16,592-A14716	Amendment approved 16/11/20
2019–16,592-A14730	Amendment approved 04/01/21
2019–16,592-A14761	Amendment approved 23/03/21
2019–16,592-A14786	Amendment approved 07/07/21
2019–16,592-A14802	Amendment approved 13/09/21
2019–16,592-A14843	Amendment approved 25/11/21

### Benefits and risks

If successful, the Stand Together trial will result in the following benefits:Reduction of bullying, which will be of benefit to all participants, victims and bullies, the whole school, local community, and society in general.Reductions in poor mental health (enhanced emotional well-being) and improved quality of life for students.Evidence on the costs and cost effectiveness of the KiVa programme in the UK.Evidence regarding programme impact on inequalities by testing whether the intervention is effective across the socio-economic gradient.Benefits to school staff through increased training and improved school environment, which may improve staff well-being.Benefits to students who participate in the intervention through opportunities for learning and improved self-efficacy.

There are no anticipated risks to participants or schools. However, there may be unanticipated events and we will actively seek evidence of any adverse effects in the process evaluation and trial data. Should any member of the research team become concerned at any point about issues in relation to any individual student, staff will follow a study-specific Standard Operating Procedure for dealing with harm that will be explained to head-teachers during the consent process and highlighted explicitly in school information sheets.

The introduction of KiVa may replace the use of other Personal Social Education (PSE) strategies or interventions to reduce bullying. However, KiVa has been trialled in several countries (e.g., Finland [11], Italy [17] and the Netherlands [18] and found to be effective (with varying levels of effectiveness), and it is unlikely to be detrimental. KiVa is presently one of only four bullying interventions with a Blueprints for Violence Prevention classification as having evidence of effectiveness (http://blueprintsprograms.com). The risks are therefore considered minimal and the anticipated benefits justify the risks.

